# Effectiveness of off-the-shelf footwear in reducing foot pain in Australian Department of Veterans’ Affairs recipients not eligible for medical grade footwear: study protocol for a randomized controlled trial

**DOI:** 10.1186/1745-6215-14-106

**Published:** 2013-04-23

## Abstract

**Background:**

Foot pain is highly prevalent in older people, and in many cases is associated with wearing inadequate footwear. In Australia, the Department of Veterans’ Affairs (DVA) covers the costs of medical grade footwear for veterans who have severe foot deformity. However, there is a high demand for footwear by veterans with foot pain who do not meet this eligibility criterion. Therefore, this article describes the design of a randomized controlled trial to evaluate the effectiveness of low cost, off-the-shelf footwear in reducing foot pain in DVA recipients who are currently not eligible for medical grade footwear.

**Methods:**

One hundred and twenty DVA clients with disabling foot pain residing in Melbourne, Australia, who are not eligible for medical grade footwear will be recruited from the DVA database, and will be randomly allocated to an intervention group or a ‘usual care’ control group. The intervention group will continue to receive their usual DVA-subsidized podiatry care in addition to being provided with low-cost, supportive footwear ([name]®, Vasyli Medical, Labrador, Queensland, Australia). The control group will also continue to receive DVA-subsidized podiatry care, but will not be provided with the footwear until the completion of the study. The primary outcome measure will be pain subscale on the Foot Health Status Questionnaire (FHSQ), measured at baseline and 4, 8, 12 and 16 weeks. Secondary outcome measures measured at baseline and 16 weeks will include the function subscale of the FHSQ, the Manchester Foot Pain and Disability Index, the number of DVA podiatry treatments required during the study period, general health-related quality of life (using the Short Form 12® Version 2.0), the number of falls experienced during the follow-up period, the Timed Up and Go test, the presence of hyperkeratotic lesions (corns and calluses), the number of participants using co-interventions to relieve foot pain, and participants’ perception of overall treatment effect. Data will be analyzed using the intention-to-treat principle.

**Discussion:**

This study is the first randomized controlled trial to evaluate the effectiveness of off-the-shelf footwear in reducing foot pain in DVA recipients. The intervention has been pragmatically designed to ensure that the study findings can be implemented into policy and clinical practice if found to be effective.

**Trial registration:**

Australian New Zealand Clinical Trials Registry: ACTRN12612000322831

## Background

Foot pain affects approximately one in three people over the age of 65 years [1-3] and has a significant impact on quality of life in this age-group. Studies of older people have demonstrated that foot pain is associated with decreased ability to undertake activities of daily living [4-9], problems with balance and gait [7,10,11] and an increased risk of falls [12-16]. Furthermore, several clinic-based studies assessing health-related quality of life across a range of age-groups have shown that people with foot disorders (such as generalized foot pain [2,17], nail infections [18-20], hallux valgus [21,22] hallux rigidus [23] and plantar heel pain [24]) demonstrate significantly lower scores than those without these conditions. A range of risk factors for foot problems has been identified, including increased age [25-27], female sex [7,8,26,28], obesity [8,10,28,29], and chronic conditions such as osteoarthritis and diabetes [8,10,29].

In addition to these risk factors, there is also strong evidence that many older people wear inappropriate or poor quality footwear, and that ill-fitting footwear may contribute to foot problems. A household survey of people aged over 80 years conducted in the United Kingdom found that most wore slippers all day, irrespective of whether they were housebound [30]. Similarly, a survey of the indoor shoe-wearing habits of 128 older people in Australia indicated that more than half spent less than 30 Australian dollars on their indoor footwear (most commonly slippers), replaced them infrequently, and often wore their indoor shoes for outdoor activities [31]. More recently, a survey of sub-acute aged care hospital patients reported that only 14% wore ‘safe’ footwear, with the most commonly observed detrimental features being a lack of fastening (86%), slippery soles (86%) and an excessively flexible heel counter (77%) [32].

By far the most commonly encountered problem with footwear in older people is the wearing of shoes that are too small. Burns *et al*. [33] compared the length and width of the feet and shoes of 65 people aged between 64 and 93 years attending a rehabilitation ward in the United Kingdom, and reported that 72% wore shoes of an incorrect size. Similarly, a study of 440 Veterans’ Affairs patients in the United States reported that only 26% were found to be wearing appropriately sized shoes [34], and a recent study of 213 people aged 60 to 80 years in Thailand reported that 50% of women and 34% of men wore shoes that were too narrow [35]. Several factors may be responsible for this, including fashion influences (particularly in older women [36,37]), not measuring foot dimensions when purchasing shoes [31], or the absence of commercially-available, low-cost footwear that adequately caters for the altered morphology of the elderly foot [38,39]. Irrespective of the underlying cause of poorly-fitting footwear, there is evidence that wearing shoes that are too small is associated with foot problems. In older people, wearing shoes substantially narrower than the foot is associated with corns on the toes, hallux valgus deformity and foot pain, whereas wearing shoes shorter than the foot is associated with lesser toe deformity [40]. Furthermore, a survey of 227 older women revealed that 61% reported foot pain when wearing shoes (most commonly in the forefoot and toes), and that those with foot pain exhibited a broader forefoot than those without pain [41].

In Australia, the Department of Veterans’ Affairs (DVA), as part of the Rehabilitation Appliances Program, covers the costs of medical grade footwear for veterans who have severe foot deformity (defined as feet that cannot be accommodated in regular ‘off-the-shelf’ footwear). Footwear provision is one of the most common podiatry interventions. An analysis of 1996 to 1997 DVA data indicated that out of the total podiatry DVA population who had received a podiatry intervention (n = 4,418), 3,227 (73%) received new medical grade footwear [42]. However, there is also a high demand for footwear by veterans who have foot pain but do not have severely deformed feet. In this context, it is likely that there are a substantial number of veterans who could benefit from the provision of more appropriate footwear. Such an intervention may also reduce the need for frequent, on-going maintenance foot care provided by podiatrists under the DVA scheme.

Therefore, the aim of this study is to evaluate the effectiveness of relatively low-cost but good quality, custom-fitted footwear to DVA clients with foot pain who do not currently meet the structural deformity criteria for medical grade footwear.

## Methods

The trial has been registered on the Australian New Zealand Clinical Trials Registry (ACTRN12612000322831).

### Ethical approval

The Australian DVA Human Research Ethics Committee provided ethical approval (approval number E012/005[5.1]) and the La Trobe University Human Ethics Committee formally accepted this approval (E012/004). All participants will provide written informed consent prior to enrolment. Ethical standards will adhere to the National Health and Medical Research Council (NHMRC) National Statement [43] and the World Medical Association's Declaration of Helsinki [44]. Publications associated with the trial will be formatted according to the Consolidated Standards of Reporting Trials (CONSORT) 2010 statement [45,46].

## Design

This study is a two-group randomized controlled trial with a 16 week prospective follow-up (Figure 1). Participants will be randomly allocated to either a ‘usual care’ control group or the intervention group [47]. Permuted block randomization with random block sizes (stratified by sex [48]) will be undertaken using an interactive voice response telephone service provided by the NHMRC Clinical Trials Centre at the University of Sydney, New South Wales, Australia to ensure allocation concealment. Due to the nature of the intervention, it will not be possible to blind the participants or investigators. However, the primary outcome measure is administered as a self-completion questionnaire and will be entered into the database by an investigator blinded to group allocation.

**Figure 1 F1:**
[figure not shown]
Trial profile.

### Participant recruitment, screening and eligibility criteria

The geocoding feature of the DVA database will be used to identify veterans currently receiving podiatry treatments who are residing in Melbourne, Victoria. From this group of veterans, the DVA Departmental Management Information System will be used to identify those who have not been issued with medical grade footwear within the last five years, by excluding veterans who have documented a footwear-related item number during this period (item numbers F604, F605, F606, F611, F612, F625, F660, F661 F670, F671, F615 or F616). The remaining veterans will form the primary recruitment source and will be mailed an information package about the study, along with an invitation to contact the research team by either return mail or by telephone. Database recruitment will be complemented by running advertisements in DVA newsletters and placing posters at Returned and Services Leagues Clubs in the surrounding suburbs.

During the initial telephone contact with participants, a member of the research team will determine each veteran’s eligibility by structured interview. To be included in the study, veterans will need to meet the following inclusion criteria:

(i) be aged 65 years or over;

(ii) be a current DVA Gold Card client not eligible for   medical grade footwear;

(iii) have received podiatry treatment on at least three   occasions in the past five years;

(iv) have disabling foot pain, using the case definition   of  the Manchester Foot Pain and Disability Index   (MFPDI) [49] proposed by Roddy *et al*. [50]. The   MFPDI consists of 19 statements prefaced by the   phrase ‘Because of pain in my feet’, formalized   under three constructs: functional limitation (10   items), pain intensity (five items), and personal   appearance (two items), with three possible   answers: ‘none of the time’ (score = 0), ‘some days’   (score = 1), and ‘most days/every day’ (score = 2).   The Roddy *et al*. definition requires at least one of   the ten functional limitation items to be documented   on most/every day(s) in the last month;

(v) have persistent foot pain, defined as foot pain   present for at least 12 weeks, and;

(vi) be capable of understanding the English language   in verbal and written form.

Veterans will not be eligible for inclusion in the study if they:

(i) are currently residing in a residential aged care   facility;

(ii) have diabetes and a history of foot ulceration (or   current foot ulceration) or diabetic peripheral   neuropathy (diagnosed with the 5.07 Semmes- Weinstein monofilament, using the International   Working Group on the Diabetic Foot protocol [51]);

(iii) have a neurodegenerative disorder (for example,   Parkinson’s disease);

(iv) have had a lower limb or partial foot amputation   (although single toe amputations will be permitted);

(v)  have been prescribed contoured foot orthoses   within the past three months (although simple flat   insoles will be permitted, as will contoured foot   orthoses prescribed more than three months ago);

(vi) are currently wearing the intervention footwear, or;

(vii)  have cognitive impairment (defined as a score of <   7 on the Short Portable Mental Status   Questionnaire [52]).

### Intervention group

The intervention group will continue to receive regular podiatry treatment as clinically required. This will typically include toenail maintenance and scalpel debridement of hyperkeratotic lesions (corns and calluses). In addition, they will be provided with good quality, off-the-shelf footwear ([name]® Vasyli Medical, Labrador, Queensland, Australia). Men will receive the ‘Brian’ style and women will receive the ‘Annie’ style (see Figures 2 and 3). Both styles are available in three width fittings (medium, wide, extra-wide) and feature a stretchable Lycra® upper with Velcro® closure and a removable, flat cushioned insole. These shoes have been selected as they meet all commonly-used criteria for appropriate footwear (such as a low heel, appropriate fixation and adequate depth to accommodate toe deformities) [53-57]. Due to sex differences in foot dimensions (and therefore the dimensions of the lasts the shoes are constructed from) the ‘Brian’ style has a relatively broader fit than the ‘Annie’ style. However, both the heel height and toe spring are the same for shoes of equivalent length across the two styles.

**Figure 2 F2:**
[figure not shown]
[name]® footwear to be used in the study for men (‘Brian’ style).

**Figure 3 F3:**
[figure not shown]
[name]® footwear to be used in the study for women (‘Annie’ style).

The research staff will measure participants’ feet using a Brannock Device® (Brannock Device Co, Inc., Liverpool, New York, USA) to ensure appropriate length and width, using the fitting protocol recommended by the footwear manufacturer [58]. Intervention group participants who wear flat insoles (or have been wearing contoured foot orthoses for more than three months) in their current footwear will be permitted to wear them in their study footwear, provided that the fit of the shoes is considered to be appropriate.

### Control group

The control group will continue to receive regular podiatry treatment as clinically required. This will typically include toenail maintenance and scalpel debridement of hyperkeratotic lesions (corns and calluses). Upon completion of the trial, they will be provided with the same footwear used in the intervention group.

### Baseline assessments

Participant characteristics will be collected by structured interview at the baseline assessment and will include age, sex, height, weight, waist circumference, hip circumference, country of birth, education, major medical conditions, medications, use of walking aids and cigarette smoking history. The following questionnaires and clinical tests will also be administered:

(i) foot pain characteristics, including duration (in months) and location, using a standardized foot diagram;

(ii) presence and severity of hallux valgus, assessed using the Manchester Scale [59];

(iii) foot structure and presence of hyperkeratotic lesions (corns and calluses), documented with three-dimensional clinical photographs using the FotoScan™ 3D foot scanner (Precision 3D Limited, Weston-super-Mare, UK);

(iv) the Pain Catastrophizing Scale, a questionnaire containing 13 items reflecting elevated negative cognitive responses to pain [60];

(v) the short version of the Geriatric Depression Scale, a 15-item depression screening tool that has been specifically validated in older people [61,62];

(vi)  footwear assessment, using selected components of the recently developed Footwear Assessment Tool [57], and;

(vii)  physical activity levels, using the Incidental and Planned Activity Questionnaire [63].

In addition, participants allocated to the footwear intervention group will be asked to complete six 100 mm visual analogue scales to ascertain their perceptions of: (i) the immediate level of comfort of the footwear (using the anchors ‘extremely uncomfortable’ and ‘extremely comfortable’ [64]); (ii) the attractiveness of the footwear (using the anchors ‘extremely unattractive’ and ‘extremely attractive’); (iii) how attractive they think other people would find the footwear (using the anchors ‘extremely unattractive’ and ‘extremely attractive’); (iv) how well the shoes fit (using the anchors ‘poorest fit possible’ and ‘best fit possible’); (v) how easy it is to put the shoes on and take them off (using the anchors ‘most difficult as possible’ and ‘as easy as imaginable’) and; (vi) how heavy the shoes are (using the anchors ‘extremely light’ and ‘extremely heavy’).

The perceived therapeutic value of the shoes will be assessed using responses to the statement ‘I believe that the shoes provided to me can reduce the severity of my foot pain’, with a five-point Likert scale ranging from ‘strongly disagree’ to ‘strongly agree’. In addition, two 100 mm visual analogue scales will be used to ascertain expectations of pain reduction associated with the footwear, with the questions ‘With your shoes, do you expect to have less or more pain in the skin of your feet and/or ankles, during activities like standing and/or walking?’ and ‘With your shoes, do you expect to have less or more pain in the muscles and joints of your feet and/or ankles, during activities like standing and/or walking?’, both using the anchors ‘much less’ and ‘much more’. These questions are derived from the Monitor Orthopedic Shoes questionnaire [65], and will be used to predict adherence to, and effectiveness of, the footwear intervention at the completion of the study.

### Primary outcome measure

The primary outcome measure will be the pain domain of the Foot Health Status Questionnaire (FHSQ). The FHSQ consists of 13 questions reflecting four foot health-related domains: foot pain, foot function, footwear, and general foot health [66]. The FHSQ pain domain comprises four questions, with higher scores representing better foot health (that is, 100 = best foot health and 0 = worst foot health). The FHSQ pain domain demonstrates a high degree of content, criterion, and construct validity (Cronbach α = 0.88), high retest reliability (intraclass correlation coefficient = 0.86) and has been used as an outcome measure in clinical trials for a range of foot disorders [67]. Previous research indicates that the minimal important difference for this measure is 12.5 points [68]. The FHSQ pain domain will be measured at baseline and at 4, 8, 12 and 16 weeks, with the primary endpoint being the 16 week score.

### Secondary outcome measures

Secondary outcome measures will be documented at baseline and 16 weeks and will include:

(i) the function domain of the FHSQ [3];

(ii) the functional limitation, pain intensity and concern about appearance subscales of the MFPDI [49];

(iii) the number of DVA podiatry treatments required during the study period;

(iv) general health-related quality of life, assessed with the Short Form 12® Version 2.0 [69];

(v) the number of falls experienced during the follow-up period;

(vi) functional mobility, using the Timed Up and Go test [70];

(vii) presence of hyperkeratotic lesions (corns and calluses);

(viii) number of participants using co-interventions to relieve foot pain (such as oral non-steroidal antiinflammatory medications, topical medications and visits to other health-care practitioners), documented using a diary at 4, 8, 12 and 16 weeks, and;

(ix) participants’ perception of overall treatment effect at week 16, assessed with the question ‘Overall, how has your foot pain changed since the start of the study?’ with a five-point Likert scale response (‘marked worsening’, ‘moderate worsening’, ‘same’, ‘moderate improvement’, or ‘marked improvement’). For the purpose of analysis, this scale will then be dichotomized, where ‘success’ is defined as marked or moderate improvement on this scale.

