### Complications and adverse events

Complications and adverse events associated with the intervention are unlikely. However, the questionnaires at the 4, 8, 12 and 16 week follow-ups will provide participants with an opportunity to report any difficulties they have with the footwear, and all adverse events will be reported in the final manuscript.

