### Statistical analysis

Statistical analysis will be undertaken using SPSS version 20.0 (IBM Corp, NY, USA). All analyses will be conducted on an intention-to-treat principle using all randomized participants. Multiple imputation will be used to replace any missing data using five iterations, with age, baseline scores, and group allocation as predictors [72]. Demographic characteristics and baseline data will be summarized by descriptive statistics. Continuous data will be explored for normality using standard tests to satisfy the assumptions of parametric statistics. If data are found to be not normally distributed, transformation will be attempted using conventional techniques [73]. However, if data are still not normally distributed after transformation, non-parametric statistical tests will be used. Continuously-scored primary and secondary outcome measures with a normal distribution will be compared between groups using a linear regression technique with baseline scores, adjusted for by the analysis of covariance model [74,75]. Nominal and ordinal scaled data will be compared using chi-square analyses (or Fisher's exact test where appropriate) and Mann–Whitney *U*-tests, respectively. Effect sizes will be determined using Cohen’s *d*[76] for continuous data and relative risks for nominal data. Statistical significance for hypothesis tests will be set at the conventional level of α = 0.05.

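### Falls and podiatry treatments are event counts, but the analysis rules lead them to a rank test with no rate ratio and no allowance for unequal follow-up

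*Protocol article*

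**What the plan says.** Under Secondary outcome measures the lead-in is "Secondary outcome measures will be documented at baseline and 16 weeks and will include". The list that follows includes "the number of DVA podiatry treatments required during the study period" and "the number of falls experienced during the follow-up period". One item, co-interventions, has its own schedule: it is "documented using a diary at 4, 8, 12 and 16 weeks". Falls and podiatry treatments have none, and the source of the podiatry count is not given.

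Under Statistical analysis, continuous outcomes with a normal distribution go to linear regression adjusted for the baseline score. For the rest, "If data are found to be not normally distributed, transformation will be attempted using conventional techniques", and a non-parametric test is used if that fails. Nominal data go to chi-square or Fisher's exact test and ordinal data to Mann-Whitney. Effect sizes are Cohen's d for continuous data and relative risk for nominal data. Missing data are multiply imputed from age, baseline scores and group. No count model, follow-up-time term or rate ratio appears.

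**The concern.** Neither count fits a rule that has been fixed. A count of events during follow-up has no baseline value of the same measure, and the article describes no retrospective one, so the baseline-adjusted ANCOVA has no defined covariate. Falls over 16 weeks will be mostly zeros, and no transformation makes such data normal, so the rule ends in a rank test. That test treats a participant seen for ten weeks like one seen for sixteen and yields no estimate of how much the event rate changed. Neither effect size in the plan expresses a difference in event rates.

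This matters most for podiatry use. The Background suggests that footwear may reduce the need for ongoing podiatry care, and the Trial status section says that the findings will inform DVA footwear provision. A p-value cannot tell the DVA what proportion of treatments is avoided.

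A related point is how falls are ascertained. If they are asked about only at week 16, recall is long, in unblinded participants aged 65 or over, and the time observed on people who leave early is lost.

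**Working it through.** **The plan's own figure.** Inputs from Sample size: difference 12.5, SD 23, power 80%, drop-out 10%. Alpha is 0.05, taken as two-sided. n = 2 × (1.96 + 0.8416)² × 23² / 12.5² = 2 × 7.849 × 529 / 156.25 = 53.2, so 54 per group; 54 / 0.90 = 60. The stated 60 per group is reproduced. It concerns FHSQ pain only.

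**Assumptions.** The article gives no event rates for the two counts, so every rate, dispersion and rate ratio below is assumed. Counts are gamma-Poisson with 54 per group. Follow-up is 16/52 = 0.308 year.

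**Share of zeros for falls.** At 1 fall per person-year the mean is 0.308. With dispersion 1, P(0) = 1 / (1 + 0.308) = 76% in the control group.

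**Precision for falls.** SE(log RR) = √{[(1/μ + d) + (1/(μ·RR) + d)] / 54}. With μ = 0.308, RR = 0.64 and d = 1, this is √[(4.25 + 6.08) / 54] = 0.437. The 95% CI then runs from the estimate divided by exp(1.96 × 0.437) = 2.36 to the estimate multiplied by it. For 80% power, n = 7.849 × 10.33 / (ln 0.64)² = 7.849 × 10.33 / 0.1992, about 408 per group. Over 0.6 to 1.5 falls per year and dispersion 0.5 to 2, the CI factor is 2.0 to 3.1 and n is 259 to 705 per group.

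**Power, unadjusted tests** (1,000 simulated trials per scenario, Monte Carlo error about 1.5 points):

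| Outcome and assumption | Negative binomial | Mann-Whitney |
|---|---|---|
| Falls, RR 0.64 | 14-26% | 11-22% |
| Falls, RR 0.5 | 21-45% | 18-42% |
| Podiatry, mean 2 or 3, dispersion 0-0.5, RR 0.8 or 0.7 | 23-84% | 19-82% |

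Scenario by scenario, the count model gains about 2 to 9 points for falls and -1 to +8 for podiatry. Part of the falls gain reflects a slightly liberal test (simulated size 4.9-6.6%). A t-test comes within about 4 points of the negative binomial.

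**Adding a prior podiatry count** (mean 2 visits, RR 0.7, 800 trials; prior-year mean 6.5 = 2 × 52/16, with the same person-level rate in both periods, which favours adjustment):

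| Method | Dispersion 0.3 | Dispersion 0.5 |
|---|---|---|
| Mann-Whitney | 44% | 34% |
| Robust Poisson, unadjusted | 50% | 43% |
| Robust Poisson, adjusted | 59% | 60% |
| Linear ANCOVA, same covariate | 57% | 58% |

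The model alone adds 50 - 44 = 6 and 43 - 34 = 9 points. The covariate adds a further 59 - 50 = 9 and 60 - 43 = 17. Linear ANCOVA with the same covariate is 2 points behind. A repeat simulation gave 36-44%, 44-50%, 57-58% and 55-56% for the four rows.

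**Person-time at stake for falls.** Planned drop-out is 10% of 120 = 12 people. If all left at week 10, 12 × 10 = 120 person-weeks would be lost under week-16-only recording, against 108 × 16 = 1,728 from completers, or about 7%.

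**The case against.** The strongest reply is that these are two of nine secondary outcomes, that a count model is a routine SAP detail, and that a condensed article may leave the ascertainment of falls to the full protocol. The first part limits the weight of the point. The second does not remove it, because the Statistical analysis section already fixes a path, and that path does not suit counts.

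Four stronger readings are tempting, and the article does not support them.

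- **Falls are collected only once.** This is the natural reading, not a statement. The lead-in cannot be literal for every item: falls during follow-up cannot be recorded at baseline, and co-interventions depart from it. Four-weekly forms exist: "the questionnaires at the 4, 8, 12 and 16 week follow-ups will provide participants with an opportunity to report any difficulties" with the footwear.
- **Podiatry counts are incomplete.** Their source is not stated, and nothing ties them to attendance at week 16.
- **Prior podiatry counts are already in hand.** The criterion "have received podiatry treatment on at least three" occasions in five years is among those checked by telephone interview. The database is described as identifying current podiatry users and screening footwear item numbers, not as supplying treatment counts.
- **The rank test wastes much power.** The gain from the model alone is small. A large gap appears only when an unadjusted rank test is set against a regression with a prior-count covariate that the article does not show to be collected.

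Nor are early leavers simply dropped, since the plan imputes missing data. But on the week-16 reading, a leaver's whole falls count would be imputed from age, baseline scores and group, with no use of the weeks actually observed.

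**Conclusion.** The concern holds as one of method and reporting. Followed as written, the rules give skewed counts, falls in particular, a rank-test p-value with no rate ratio and no allowance for unequal follow-up. A count model with a time offset corrects this cheaply. The power gain from the model itself is roughly 0 to 9 percentage points under the assumed rates, so power is not the reason to change. Falls cannot be tested with useful power in this trial under any of the methods tried: at an assumed rate ratio of 0.64 they would need some 259 to 705 per group. The value there is an estimate with an honest, wide interval. The falls-recording point rests on the most natural reading of the secondary outcome list and would fall away if the full protocol shows four-weekly recording. The primary outcome, the sample size and the main conclusion are untouched.

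**What to change.** - Analyse falls and DVA podiatry treatments with negative binomial (or robust Poisson) regression, with log follow-up time as offset and adjustment for sex, the stratification factor. Report rate ratios with 95% CI.
- Label falls exploratory.
- State how this fits with the multiple-imputation rule, since the offset already uses the time observed on early leavers.
- Name the source of the podiatry count. Adjust for prior DVA treatment counts only if they can be obtained from DVA records.
- Ask about falls on the existing 4, 8, 12 and 16 week forms. This shortens recall and keeps the person-time of those who leave early.

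The cost is one extra question on each form, a few sentences of analysis text and a little more analysis work.

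### Corns and calluses are scored as present or absent, so a partial reduction in lesions does not register; if lesions are common, a count would be considerably more powerful

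*Protocol article*

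**What the plan says.** Item (vii) under Secondary outcome measures in the protocol article is the "presence of hyperkeratotic lesions (corns and calluses". The lead-in to that list fixes the timing: "Secondary outcome measures will be documented at baseline and 16 weeks and will include". Baseline assessments, item (iii), uses the same scale: "foot structure and presence of hyperkeratotic lesions (corns and calluses), documented with three-dimensional clinical photographs". Two other items in the secondary list, podiatry treatments (iii) and falls (v), are worded as numbers of events. Item (vii) is not.

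Presence is nominal, and the Statistical analysis section says "Nominal and ordinal scaled data will be compared using chi-square analyses (or Fisher's exact test where appropriate", with effect sizes given as "relative risks for nominal data". No reason is given for cutting at zero, and the unit of scoring (participant, foot or site) is not stated.

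No prevalence is given either. There are two indirect hints. The eligibility criteria require at least three podiatry treatments in the past five years. The description of usual podiatry care, the same in both arms, reads "This will typically include toenail maintenance and scalpel debridement of hyperkeratotic lesions (corns and calluses".

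**The concern.** Presence is a lesion count cut at zero. If each participant receives one yes/no score, someone who goes from four lesions to one is recorded as unchanged, and only complete clearance counts as benefit. The more common lesions are, the more of the treatment effect lies above the cut.

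The outcome matters to the trial's argument. The Background links narrow shoes to corns on the toes and hopes that better footwear will reduce maintenance foot care. In a trial where participants cannot be blinded, it is also one of the few outcomes observed on the foot rather than self-reported. At stake is a non-significant result on item (vii) while the shoes have in fact reduced the number of lesions.

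The choice also cannot be undone later. Presence can always be derived from a count, but a count cannot be recovered from a recorded yes or no.

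**Working it through.** **Number analysed.** The Sample size section gives a difference of 12.5, SD 23, 80% power and 10% drop-out. With two-sided alpha 0.05 (sidedness is not stated):

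n = 2 × (1.96 + 0.8416)² × 23² / 12.5² = 53.1, rounded up to 54 per group; 54 / 0.9 = 60.

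This reproduces the stated 60 per group. With 54 analysed, power for the primary outcome is 80.6%. The article claims no power for item (vii). The same 54 per arm is used below.

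**Assumed inputs, none of them in the article.** Lesion counts are negative binomial with mean μ and shape k, or Poisson. The footwear group's mean is 30% or 50% lower. Then P(any lesion) = 1 − (k / (k + μ))^k.

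**Example.** For μ = 2.5 and k = 2, presence in controls is 1 − (2/4.5)² = 80%. A 40% cut in the mean (μ = 1.5) gives 1 − (2/3.5)² = 67%. So a 40% fall in lesions appears as a fall of only 13 percentage points in presence. For 80% power at 54 per arm, presence would have to fall from 80% to about 55%, from 90% to about 68%, or from 50% to about 24%.

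**Power (%), presence v count.** Presence: two-proportion power formula. Count: Mann-Whitney test, 1000 simulated trials per cell.

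| Control prevalence | Shape k | 30% cut | 50% cut |
|---|---|---|---|
| 50% | 1 | 14.8 v 18.7 | 41.8 v 53.9 |
| 50% | 2 | 18.1 v 23.6 | 50.4 v 59.7 |
| 50% | Poisson | 22.5 v 26.1 | 59.7 v 68.3 |
| 80% | 1 | 11.8 v 27.2 | 34.5 v 75.9 |
| 80% | 2 | 18.2 v 37.2 | 54.9 v 88.8 |
| 80% | Poisson | 30.9 v 54.5 | 79.2 v 95.8 |
| 90% | 1 | 8.6 v 33.1 | 22.9 v 82.4 |
| 90% | 2 | 14.4 v 47.0 | 44.8 v 95.7 |
| 90% | Poisson | 30.3 v 69.1 | 79.9 v 99.4 |

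**Loss from using presence.**
- At 80-90% prevalence: from 27.2 − 11.8 = 15.4 points to 82.4 − 22.9 = 59.5 points.
- At 50%: from 26.1 − 22.5 = 3.6 points to 53.9 − 41.8 = 12.1 points. The simulation error near the lower end is √(0.26 × 0.74 / 1000) = 1.4 points. Longer runs put the range at about 5 to 12.
- At 30%: 0 to 3 points in further runs of the same model.

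**Counting error.** In the case μ = 2.5, k = 2, power for presence is about 19%, 33% and 54% for cuts of 30%, 40% and 50%. The count gives 39%, 66% and 88%. When counts carry a random one-lesion miscount, power is still 36%, 62% and 84%.

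**The case against.** The strongest objection is that the size of the loss rests on a prevalence the article never gives. Three podiatry visits in five years is fewer than one a year. Toenail care alone would satisfy that criterion, and eligibility rests on foot pain of any cause, not on skin lesions. Debridement continues in both arms and may itself lower what is visible at 16 weeks. A reader might infer that presence is near its ceiling; the article does not show this, and at 30% prevalence a count gains almost nothing. This stands, and the conclusion is conditional on it.

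Second, scoring per participant is an inference. Presence per foot or per site would register some partial change, and a journal article may leave such detail to the full protocol. This also stands. But the scale itself is stated as presence, in both places where lesions appear as a measurement, so the point disputes a stated choice and does not ask for absent detail.

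Third, a reader might infer that any fall in lesion number is invisible, or that a null result could not be interpreted. Neither is supported. Full clearances register, and presence has 55% power for a halving at 80% prevalence with k = 2. In that setting the count itself has only 37% power for a 30% cut, so a null on the count could also be inconclusive.

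Fourth, the simulation assumes a uniform proportional reduction, and adjoining calluses are hard to count. The miscount check shows that most of the gain survives random error. A count still says nothing about lesion size or severity.

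Fifth, a reader might infer that the count can be read from scans already planned. The 3D photographs are listed only under Baseline assessments, and the article does not say that they are repeated at 16 weeks.

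Finally, the hope of less maintenance care is measured directly by secondary outcome (iii), the number of podiatry treatments. That is a different outcome and does not stand in for lesion burden.

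**Conclusion.** The point holds in a conditional form. As worded, item (vii) records presence. On the natural per-participant reading, only full clearance (or a first appearance) of lesions can change a participant's score. If lesions are common, as a podiatry-treated population suggests without proving, the loss of power against a count is substantial: roughly 15-60 points at 80-90% prevalence. It is modest at 50% (about 5-12 points) and negligible at 30%. These figures assume 54 analysed per arm, a two-sided 5% test, negative-binomial or Poisson counts and a 30-50% proportional reduction.

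This is a cheap improvement to one of nine listed secondary outcomes. It is not a flaw in the primary analysis, and the 60 per group reproduces exactly.

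**What to change.** At the baseline and 16-week assessments that the secondary outcome list already requires, record the number of hyperkeratotic lesions (corns plus calluses, both feet). Compare the 16-week count between groups with a negative-binomial model or, at minimum, the Mann-Whitney test that the Statistical analysis section already names. Keep presence per participant, with its relative risk, as a descriptive summary; this also settles the unit of scoring.

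The change is one line in the outcome definition and one in the analysis section. It costs a short extra count at each assessment and some reader variability, for which a simple rule on adjoining calluses should be written down. The count should be made at the assessment itself and should not depend on 16-week 3D scans, which the article does not state. No additional participants or visits are needed.
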